### Recruitment

Participants will be recruited from metropolitan, suburban, and rural regions in New Mexico to ensure representation of families from diverse geographic, ethnic, and socioeconomic backgrounds. Recruitment will use a multimodal strategy that includes an informational study website, targeted online advertising, outreach to local autism support networks, and distribution of printed materials in community settings. Partnerships with pediatric and behavioral health providers will support referral-based recruitment. All recruitment materials and advertisements will be reviewed and approved by the Stanford University IRB before use. Interested caregivers will be directed to a secure REDCap link to complete the preliminary screening survey.

### Allocation

#### Sequence Generation

Randomization will be conducted in REDCap using a randomization code with an allocation ratio of 1:1:1 and a block size of 6. The study statistician will generate the randomization code and provide the randomization schedule to an independent REDCap administrator, who will upload the randomization scheme into the secure REDCap randomization module.

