### Trial Design

The Caregiver Outreach Autism Coaching at Home study is a single-site, multiarm, parallel-group, randomized controlled superiority trial targeted to decrease challenging behaviors in children with ASD. We aim to recruit 90 caregiver-child dyads to participate in the 4-year study. Each dyad will first receive a practical functional assessment (PFA) to identify the function(s) of the child’s challenging behavior and subsequently randomized (1:1:1) to telehealth-delivered SBT, in-person SBT, or online psychoeducation.

The primary outcome will be in-session rates of challenging behavior observed at the 12-week outcome point, measured through standardized behavioral observation procedures as well as reported levels of caregiver stress. Secondary outcomes will include family quality of life, treatment satisfaction, and indicators of sustained family engagement and continuity of care, reflected by the number of scheduled sessions completed, missed appointments, and participant attrition at the 12-week outcome (end of treatment). A SPIRIT (Standard Protocol Items: Recommendations for Interventional Trials) diagram showing the schedule of enrollment, interventions, and assessments is shown in he overall study is shown in Figure 1. The study flowchart is shown in Figure 2. For all participants, in-session observations and parent questionnaires will be conducted at 5 assessment points: baseline (T0), 4 weeks (T4), 8 weeks (T8), 12 weeks (T12), and 16 weeks (T16). The study protocol (version 1.9; May 8, 2025) follows the SPIRIT statement. The trial has been registered at ClinicalTrials.gov (identifier: NCT05268796). All methods were finalized before enrollment began. Subsequent protocol revisions included decreasing the lower bound of the age range to include children aged 2 years and including additional rural counties in New Mexico to increase the reach of the study.

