### Sample Size

The sample size will be 90 caregiver-child dyads, with each dyad randomized to one of three arms: (1) telehealth-delivered SBT (N_1_=30), (2) in-person SBT (N_2_=30), and (3) caregiver online psychoeducation (N_3_=30). Power estimation was based on the primary outcome, the rate of challenging behavior recorded during in-session observations. Power analyses were conducted using mixed-effects modeling, accounting for anticipated attrition of 20% by week 12. Therefore, oversampling beyond the initial total of 90 caregiver-child dyads is not planned.

Preliminary data from our prior study demonstrated a large intervention effect (Cohen *d*=1.5) on the rate of challenging behavior during in-session observations after a 12-week comparable intervention delivered via telehealth [59]. To provide a conservative estimate, we used an effect size of *d*=0.8 for our power estimation. We conservatively assumed an intraclass correlation across repeated measures of 0.7 based on the established test-retest reliability of 0.8‐0.9 for in-session observations of challenging behavior. Under these assumptions, with initial N=30 per group and 20% attrition, the estimated power to detect a significant intervention effect is 0.88 (α=.05, 2-tailed).

We further hypothesize that parenting stress, as measured by the PSI-4-SF, will be significantly lower at the 12-week assessment point among caregivers receiving telehealth-delivered SBT compared with those receiving in-person SBT. As a clinically meaningful minimum effect size, we assumed an effect size (Cohen’s *d*=0.8), which is also supported by previous studies. We assumed a 20% attrition rate by 12 weeks. Under this scenario, the estimated power to detect a group difference is 80% (2-tailed, α=.05) based on a simple group comparison. Power is expected to improve when a longitudinal mixed-effects model incorporating repeated measures is applied.

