#### Allocation Concealment Mechanism

Allocation concealment will be maintained through REDCap’s centralized randomization module, which prevents study personnel from accessing or predicting assignment prior to randomization. Because the randomization sequence is stored within the secure REDCap environment and controlled by an independent data manager, no physical allocation lists or files will be accessible to the research team. Each participant’s assignment will remain unknown until eligibility is confirmed and baseline assessments are substantially complete. This process will ensure that participant enrollment and intervention assignment remain temporally separated, prevent allocation bias, and support the timely initiation of services.

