#### Implementation

Participants will be enrolled by the study coordinator, who will assign each caregiver-child dyad to an intervention arm using REDCap’s automated randomization feature.

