#### Blinding

Because session format (telehealth vs in person) is visually apparent, blinding of participants, clinicians, and observers is not feasible. To minimize bias, observers will use standardized operational definitions, and all coders will complete extensive training and achieve ≥85% interobserver agreement (IOA) before coding. IOA will be monitored on at least 25% of coded sessions.

The study statistician and PIs will remain blinded to group allocation during data analysis. Analyses will be conducted on deidentified datasets containing only coded group labels (eg, groups A, B, and C), and the randomization key will remain with the independent REDCap administrator until all analyses are complete. Although blinding is not feasible, these procedures will minimize the risk of bias and preserve analytic integrity. Because participants, clinicians, and observers are not blinded, an unblinding procedure is not applicable. The analytic team will remain blinded to group assignment until all analyses are complete.

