## Results

The study was funded in May 2022. Participant recruitment began in January 2024 and is projected to conclude in October 2026. As of March 2026, 81 caregiver-child dyads have been enrolled, with equal allocation across the 3 study groups (27 per group; 33%). Data analysis is expected to occur between Winter 2026 and Spring 2027, with primary results anticipated in Fall 2027.

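### One stated block size of 6 in an open, single-site trial does not support the assurance that assignments cannot be predicted

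*Protocol article*

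**What the plan says.** Sequence Generation gives one ratio and one block size: "Randomization will be conducted in REDCap using a randomization code with an allocation ratio of 1:1:1 and a block size of 6". With three arms, each block holds two assignments per arm. The statistician generates the code and an independent REDCap administrator uploads it.

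Allocation Concealment Mechanism describes the module as one "which prevents study personnel from accessing or predicting assignment prior to randomization". It also says that "the randomization sequence is stored within the secure REDCap environment and controlled by an independent data manager", that the team has no access to any list, and that an assignment stays unknown until eligibility is confirmed and baseline is substantially complete.

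Three other statements bear on this. Trial Design calls the study a "single-site, multiarm, parallel-group, randomized controlled superiority trial". Implementation says: "Participants will be enrolled by the study coordinator, who will assign each caregiver-child dyad to an intervention arm". Blinding says that "blinding of participants, clinicians, and observers is not feasible".

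Results reports 81 dyads enrolled by March 2026, 27 in each group, with recruitment still open.

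**The concern.** A central module can hide the list. It cannot stop inference from assignments already made when blocks have a known size and the arms are visible. Here the coordinator operates the randomisation and so sees each assignment as it is made. The block size is printed in an article that describes recruitment as continuing.

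What is at stake is selection bias. In-person delivery needs weekly clinician travel across 19 New Mexico counties and 2 Texas counties, so staff could have a practical reason, without bad intent, to time a distant family's randomisation. Eligibility includes an investigator-judgement exclusion, and accrual is planned at 10 dyads per quarter, so a block of 6 is easy to tally. Session attendance, caregiver stress and behaviour rate are all trial outcomes. The observers who score behaviour are unblinded, so the trial leans heavily on sound allocation.

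**Working it through.** **Inputs.** Ratio 1:1:1 and block size 6 (Sequence Generation). N = 90 (Sample Size), so 90/6 = 15 blocks. Open arms (Blinding). One site (Trial Design). 27 per arm at 81 (Results). Assumptions: every block has size 6, and the observer knows this and the order of past assignments.

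**The article's own figure.** 81 = 13 × 6 + 3. Thirteen full blocks give 13 × 2 = 26 per arm, and 27/27/27 follows if the next three dyads fall one to each arm. The probability of that is 1 × 4/5 × 2/4 = 0.40. The reported split therefore fits one list in blocks of 6.

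**Predictability by position**, over the 6!/(2!·2!·2!) = 90 orderings of a block:

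| Position | Certain | At least one arm excluded | Best guess right |
|---|---|---|---|
| 1 | 0 | 0 | 2/6 = 0.333 |
| 2 | 0 | 0 | 2/5 = 0.400 |
| 3 | 0 | 1/5 = 0.20 | 2/4 = 0.500 |
| 4 | 0 | 1 − 0.40 = 0.60 | 0.4 × 1/3 + 0.6 × 2/3 = 0.533 |
| 5 | 1/5 = 0.20 | 1 | 0.2 × 1 + 0.8 × 1/2 = 0.600 |
| 6 | 1 | 1 | 1 |
| Sum | 1.2 | 2.8 | 101/30 = 3.367 |

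- Certain: 1.2/6 = 20%, or 1.2 × 15 = 18 of 90.
- At least one arm excluded: 2.8/6 = 47%, or 2.8 × 15 = 42 of 90.
- Best guess right: 3.367/6 = 56%, or 50.5 of 90, against 30 of 90 (33%) without blocking.

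**The last nine dyads**, if there is a single list used in order and all 81 enrolled dyads were randomised. Dyads 82 to 84 must be one of each arm, so 83 has an arm excluded and 84 is certain. Adding the final full block gives 1 + 1.2 = 2.2 certain and 2 + 2.8 = 4.8 with an arm excluded.

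**Alternatives.** These come from 3,000 simulated trials of 90 dyads. The observer updates by Bayes' rule and knows the possible sizes (equally likely) but not the size of each block.

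| Block sizes | Certain, of 90 | Arm excluded, of 90 | Best guess right |
|---|---|---|---|
| Fixed 6 (exact) | 18.0 | 42.0 | 56.1% |
| 3 and 6 | 7.9 | 19.8 | 57.6% |
| 3, 6 and 9 | 3.4 | 9.3 | 55.2% |
| 6 and 9 | 4.6 | 12.5 | 54.0% |
| 6, 9 and 12 | 2.2 | 6.4 | 52.6% |

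Varying the sizes removes most certain predictions but hardly changes guessing. Mixing in mainly small blocks (3 and 6) makes guessing slightly better than fixed 6.

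**The case against.** The strongest reply is that concealment in its usual sense is intact: central custody, no list open to the team, and assignment only after eligibility is confirmed. That stands. A reader might infer that the stated concealment fails altogether, and the document does not support this. Only the claim about prediction fails, and 80% of assignments are never certain.

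Several premises are also inferred. No strata are mentioned, but this is a condensed article. Blocks of 6 within strata would be predictable too, by a tally within stratum. Nor does the text say whether the coordinator knew the block size while the first 81 dyads were allocated. That stands as a limit on what can be concluded.

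A reader might also take the 27/27/27 split to prove that dyads 82 to 84 had to be one of each arm. That holds only under the conditions given in the working.

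Finally, the route to bias is narrow. Families pass through screening, consent, baseline and the functional assessment before randomisation. Accrual is under one dyad a week, so few families could be swapped. Every caregiver must accept home visits to be eligible. These points lower the likelihood of manipulation, and no evidence or size of bias is available. They do not make the sentence about prediction correct.

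**Conclusion.** The point holds in a limited form. The article claims protection against prediction that its stated allocation scheme does not give. For an observer who knows the block size and the order of past assignments, 18 of 90 assignments are certain, at least one arm can be excluded for 42 of 90, and the best guess is right 56% of the time instead of 33%. These figures rest on a constant block size of 6, the only one stated, and on that observer's knowledge, which the article does not settle. They measure predictability, not bias. Nothing in the document shows that any family was timed or selected by expected arm.

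**What to change.** 1. In Allocation Concealment Mechanism, remove the claim about prediction. Keep the statement that the list is inaccessible, and say that allocation used blocks of 6 and that partial prediction was possible. Cost: one sentence.

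2. For all randomised dyads, add a descriptive selection-bias check. For each dyad and arm, compute the allocation probability implied by earlier assignments in the block: places left for that arm divided by places left in the block. Set baseline behaviour rate, baseline PSI-4-SF and home location against that probability. Coded arm labels suffice, so the analysts stay blinded. Use only baseline values recorded before assignment. Power is low at N = 90, so an unremarkable result is weak reassurance. Cost: one short analysis of data already held.

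3. For any unused slots, have someone outside the enrolling team regenerate the list with randomly varying, undisclosed block sizes that are not mainly small, for example 6 and 9, or 3, 6 and 9, rather than 3 and 6. Cost: one REDCap upload and a possible small final imbalance between arms. The gain is limited, because at most 90 − 81 = 9 dyads remained in March 2026. The first two changes therefore matter most.

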#### Allocation Concealment Mechanism

Allocation concealment will be maintained through REDCap’s centralized randomization module, which prevents study personnel from accessing or predicting assignment prior to randomization. Because the randomization sequence is stored within the secure REDCap environment and controlled by an independent data manager, no physical allocation lists or files will be accessible to the research team. Each participant’s assignment will remain unknown until eligibility is confirmed and baseline assessments are substantially complete. This process will ensure that participant enrollment and intervention assignment remain temporally separated, prevent allocation bias, and support the timely initiation of services.

#### Implementation

Participants will be enrolled by the study coordinator, who will assign each caregiver-child dyad to an intervention arm using REDCap’s automated randomization feature.

#### Blinding

Because session format (telehealth vs in person) is visually apparent, blinding of participants, clinicians, and observers is not feasible. To minimize bias, observers will use standardized operational definitions, and all coders will complete extensive training and achieve ≥85% interobserver agreement (IOA) before coding. IOA will be monitored on at least 25% of coded sessions.

The study statistician and PIs will remain blinded to group allocation during data analysis. Analyses will be conducted on deidentified datasets containing only coded group labels (eg, groups A, B, and C), and the randomization key will remain with the independent REDCap administrator until all analyses are complete. Although blinding is not feasible, these procedures will minimize the risk of bias and preserve analytic integrity. Because participants, clinicians, and observers are not blinded, an unblinding procedure is not applicable. The analytic team will remain blinded to group assignment until all analyses are complete.

#### Data Collection Methods

Participants will complete questionnaires at baseline (T0), 4 weeks (T4), 8 weeks (T8), 12 weeks (T12), and at 16 weeks (4-week posttreatment follow-up [T16]). Clinical trial staff, under the supervision of the PI and site-PI, will collect all questionnaire and observational data. All clinical data will be entered directly into REDCap from the source documents by authorized study personnel to maintain data integrity.

#### Interobserver Agreement

To ensure the reliability of observational outcome measures, IOA will be calculated on 25% of all primary observation points (T0-T16). Trial-by-trial IOA will be calculated by dividing the number of agreements by the number of trials in a session block and then multiplying the quotient by 100. An agreement will be scored if both observers score the same number of behaviors in a trial. For caregiver and clinician fidelity measures, total-count IOA will be calculated by dividing the number of agreements by the total number of events in each session block and multiplying by 100. Additional session-level data collected for monitoring intervention progress will not undergo IOA scoring, as these data will not be included in the trial outcomes.

### Caregiver Fidelity of Implementation

Caregiver fidelity data will be collected during each session using a standardized checklist monitoring 3 types of events: child-led play (9 items), adult-led instruction (10 items), and transition events (5 items) (Table S1 in Multimedia Appendix 1). Fidelity will be calculated as the percentage of correctly implemented steps (number of correctly implemented steps divided by the total number of events and then multiplied by 100).

### Clinician Fidelity of Implementation

Clinician fidelity data will be collected in 10% of sessions using a standardized checklist monitoring the teaching process (Table S2 in Multimedia Appendix 1). Clinician fidelity data will be reported as the number of events correctly implemented divided by the total number of events and then multiplied by 100 to obtain the percent correct.

### Participant Retention

If a participant misses a scheduled visit, research staff will contact the caregiver, attempt to reschedule within 1 week, and emphasize the importance of maintaining the visit schedule. Up to 3 contact attempts (telephone, email, or text) will be made before a participant is considered lost to follow-up. All contact attempts will be documented in the participant’s study record.

Each caregiver-child dyad will be eligible to receive up to US $200 in honoraria for completing study assessments. US $50 gift cards will be distributed at baseline and weeks 4, 8, and 12. Families who withdraw before study completion will receive prorated compensation based on completed assessments. Participants who discontinue the intervention will not be asked to complete additional outcome measures; however, all data collected up to the point of withdrawal will be retained for analysis. Reasons for discontinuation will be documented to support transparent reporting of attrition.

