#### Criteria for Discontinuing or Modifying Allocated Interventions

Participants may withdraw from the study at any time. Investigators may discontinue a participant for (1) nonparticipation with study procedures, (2) inability to contact the family, and (3) any event, medical condition, or situation occurs such that continued data collection would not be in the participant’s best interest or may confound outcomes. For participants who remain enrolled, intervention procedures may be modified within predefined clinical parameters to ensure participant safety, accommodate individual learning needs, or maintain engagement. Consistent with the SBT framework, clinicians may adjust session pacing, reinforcement schedules, prompting procedures, visual supports, or task demands based on participant progress and caregiver feedback. For telehealth sessions, coaching methods may be tailored to caregivers’ comfort and logistical constraints. For example, the clinician may schedule brief practice segments before beginning the formal sessions with the child or provide written guidance. The targeted functional relations, the sequence of SBT phases, and the treatment dose will not be altered. Any changes that substitute non-SBT methods (eg, punishment-based procedures) will be prohibited.

If a behavior escalates to a level that compromises safety, the clinician will pause skills training and ensure that the participant returns to HRE before resuming intervention. All modifications will be reviewed in weekly supervision meetings and documented in session notes to ensure adherence to the study protocol and core SBT components.

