### Protocol Deviations and Missing Data

This protocol defines a protocol deviation as any noncompliance with the clinical trial protocol, International Council for Harmonisation Good Clinical Practice, or Manual of Procedures requirements. Noncompliance may be attributable to the participant, the investigator, or the study site staff. As a result of deviations, corrective actions will be developed by the site and implemented promptly. It will be the responsibility of the site investigator to exercise continuous vigilance to identify and report deviations within 7 working days of their identification or within 14 working days of the scheduled protocol-required activity. All deviations will be addressed in the study source documents and reported to the Department of Defense program official. We will implement rigorous efforts to minimize missing data. Nonetheless, missing data may occur due to the follow-up period. Missing data due to attrition or incomplete assessments will be handled under the assumption that data are missing at random, conditional on observed information.

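### Outcome collection ends when a dyad stops the intervention, so its week-12 outcomes are never sought and the primary contrasts rest on a missing-at-random assumption that cannot be checked

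*Protocol article*

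**What the plan says.** The Participant Retention section sets the rule: "Participants who discontinue the intervention will not be asked to complete additional outcome measures". The same sentence adds that "all data collected up to the point of withdrawal will be retained for analysis", so it treats stopping the intervention and withdrawing from the study as one event. Reasons for stopping are documented. A missed visit alone does not trigger the rule. Staff try to reschedule it within a week, and a family counts as lost only after up to three contact attempts.

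The section on criteria for discontinuing or modifying allocated interventions lets investigators discontinue a participant for nonparticipation, for loss of contact, or where an event means that "continued data collection would not be in the participant’s best interest or may confound outcomes".

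The Statistical Methods section makes the group difference at week 12 the primary parameter for both primary outcomes (rate of in-session challenging behavior and PSI-4-SF total). It is estimated by a maximum-likelihood mixed model on all available visits. On gaps in the data the plan says: "Missing data due to attrition or incomplete assessments will be handled under the assumption that data are missing at random, conditional on observed information".

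**The concern.** Whether outcomes are sought after treatment stops is a data-collection decision. A statistical analysis plan can choose how to model missing values, but it cannot recover values that nobody requested.

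Under this rule almost every observed outcome comes from a dyad still receiving its intervention. For a dyad that stops, the model predicts week 12 from its own earlier visits and from the course of dyads in its arm that continued. In effect this asks what would have happened had nobody stopped. That may differ from the effect of assigning a family to an arm, which is what families and payers would use. The prediction is sound only if stopping is unrelated to the unseen week-12 value once arm and earlier visits are known. Assessments are four weeks apart, so a family that deteriorates and leaves between two of them would break that condition without trace.

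The confounding ground adds a route by which events after randomisation can end a dyad's data. The Blinding section says that participants, clinicians and observers know the arm. The principal investigators' blinding is stated only for data analysis.

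**Working it through.** **Inputs.** "The sample size will be 90 caregiver-child dyads", with "allocation ratio of 1:1:1 and a block size of 6", gives 30 per arm (Sample Size; Sequence Generation). For challenging behavior, power was computed "accounting for anticipated attrition of 20% by week 12". For the PSI-4-SF, "We assumed a 20% attrition rate by 12 weeks". Both use d = 0.8 and two-sided alpha 0.05. The intraclass correlation for challenging behavior is 0.7.

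**1. Reproducing the stated power.** Dyads per arm with a week-12 value: 30 × (1 − 0.20) = 24.
- PSI-4-SF, simple comparison: Φ(0.8 × √(24/2) − 1.96) = Φ(0.811) = 0.791, against the stated 80%. The exact t test gives 0.774.
- Challenging behavior: the variance of a mean of m equally correlated measures is (1 + (m − 1) × 0.7)/m. For m = 4 it is 0.775 and power is 0.883; for m = 3 it is 0.80 and power is 0.873. The stated value is 0.88. The article does not say which form was used.

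The stated power therefore already allows for 20% attrition.

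**2. How many dyads.** 0.20 × 90 = 18 dyads (6 per arm) lack a week-12 value if all anticipated attrition comes from stopping the intervention. The 20% is an all-cause expectation that also covers loss of contact, and it is not a limit. The share due to stopping is not given.

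**3. What the retained data contribute.** Take four visits, equal correlation 0.7 and no baseline constraint. If all dropouts leave before week 4, the variance of an arm's week-12 mean is 0.7²/30 + (1 − 0.7²)/24 = 0.01633 + 0.02125 = 0.03758. This is worth 1/0.03758 = 26.6 complete dyads per arm. With dropout spread evenly the figure is 27.1, and if all leave after week 8 it is 27.4. Power at d = 0.8 is then 0.83 to 0.84, against 0.791 for completers only. The earlier visits do contribute, but this precision is gained under the assumption in question.

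**4. Bias if the assumption fails.** Let p be the unobserved share of an arm and δ the gap, in SD, between the true week-12 mean of those dyads and the model's prediction. The arm mean shifts by p × δ. With p = 0.20 and assumed values of δ in one arm only:

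| δ (SD) | Shift (SD) |
|---|---|
| 0.25 | 0.05 |
| 0.5 | 0.10 |
| 0.8 | 0.16 |
| 1.0 | 0.20 |

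For a contrast of arms A and B the shift is p_A δ_A − p_B δ_B. Equal shares and equal δ cancel. With assumed shares of 30% and 10% and a common δ of 0.5 SD, the shift is (0.30 − 0.10) × 0.5 = 0.10 SD.

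**5. Extreme case.** Suppose that completers gain 0.80, that the 20% who stop SBT end at control level with no sign of it at weeks 4 and 8, and that comparator dropouts follow the model. The effect in all randomised dyads is 0.80 × (1 − 0.20) = 0.64, while the model would still estimate about 0.80. If stoppers lost half the benefit (δ = 0.4), it is 0.80 − 0.20 × 0.4 = 0.72.

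**6. Reach of a change now.** By March 2026, 81 dyads were enrolled, leaving 9. At the target of 10 per quarter and 16 weeks' participation each, about 10 × 16/13 ≈ 12 were still in the study. That is roughly 20 dyads, and about 4 stoppers at 20%.

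**The case against.** The strongest case on the other side is that the plan already does much of what one would ask, and several stronger readings fail.

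- A reader might infer that these dyads are excluded from the week-12 comparison. They are not, because their earlier visits enter the likelihood.
- A reader might infer that up to 20% are affected. The 20% is an expectation for all causes and not a ceiling, and some of it is loss of contact that no change to this rule would recover.
- A reader might infer that power is lost. The stated power assumes this attrition. In the scenario where stoppers lose all benefit, the effect in all randomised dyads is 0.64, and a t test even with all 30 per arm observed has power 0.68, below the 0.774 for 24 per arm at 0.80. The case for retrieval is therefore about bias, not power.
- The Objectives expect better continuity with telehealth than in person, and a reader might infer that this alone defeats missing at random. It does not, because arm is in the model. It also says nothing about SBT against psychoeducation.
- A reader might infer a per-protocol analysis. Statistical Methods says that fidelity is studied as a mediator instead.
- A reader might infer that the benefit of SBT is overstated. The article does not establish a direction. Caregivers practise between sessions, so total loss of benefit is not the obvious case.
- The absence of a missing-data sensitivity analysis is not a finding, because it may be in an analysis plan that is not shown.

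All of this stands. It narrows the point without removing it: the rule ensures that off-intervention outcomes are not sought, and no model can check the assumption without them.

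**Conclusion.** The concern holds in limited form. By design, week-12 values of both primary outcomes go unobserved for dyads that stop the intervention, and a further ground allows discontinuation because of possible confounding. The week-12 contrast for these dyads then depends on extrapolation from those that continued.

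The plausible size is 0.05 to 0.20 SD in an arm's mean. This rests on two assumptions: that 20% of the arm is unobserved for this reason, and that the departure is 0.25 to 1.0 SD. The 0.64 against 0.80 comparison is the extreme in which all benefit is lost, not an expectation. The number of dyads affected and the direction are not known from the article.

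**What to change.** Amend the Participant Retention section so that stopping the intervention and withdrawing from assessments are separate events.

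- Keep asking every consenting dyad that is still in follow-up or yet to enrol for at least the caregiver questionnaires (PSI-4-SF and the others) through weeks 12 and 16, whether or not it still attends sessions.
- Request the observation probe only where the family agrees and it is safe. For this outcome retrieval will be harder, because the probe needs the caregiver to present an evocative condition.
- Analyse all dyads by assigned arm.
- Record potentially confounding events instead of using them as a reason to end data collection. Leave the best-interest ground as it is. The change concerns data collection only and does not touch when treatment is stopped.
- For dyads that have already stopped, report numbers and reasons by arm and limit the conclusions accordingly.

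The cost is a short amendment with consent wording and a small scheduling effort. The four US $50 payments (4 × 50 = US $200) cover baseline to week 12, so no honorarium is currently set for week 16. Some families will decline. With 81 of 90 dyads enrolled by March 2026, only the remaining enrolments and those still in follow-up can benefit, and the benefit shrinks with delay.
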